### Data and safety monitoring

Three experts on intensive care research will act as the data and safety monitoring board for the study. The predefined serious adverse events (SAE) that could be related to the treatment interventions include severe hypercapnia and respiratory acidosis (PaCO_2_ > 10 kPa and pH < 7.15), unexplained brain edema on CT scanning, and severe unexplained ARDS (PaO_2_/FiO_2_ ratio of < 100 mmHg). All these events will be recorded in the study database and reported to the study’s principal investigators within 24 h. If applicable, the study intervention will be interrupted immediately and the patient will be treated according to the standard protocol of the ICU.

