## Background

Hypoxic ischemic encephalopathy is the leading cause of morbidity and mortality after out-of-hospital cardiac arrest (OHCA) [1]. The development of neurological injury occurs during the first 48 h after cardiac arrest, with cerebral hypoperfusion being a potential mechanism [2, 3]. The levels of arterial carbon dioxide tension (PaCO_2_), arterial oxygen tension (PaO_2_), and mean arterial pressure (MAP) may be modified during this period and this may influence cerebral blood flow (CBF), cerebral oxygen delivery, and potentially the severity of the developing brain injury. The optimal targets for PaCO_2_, PaO_2_, and MAP are currently undefined [4].

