## Methods/Design

The COMACARE trial is a prospective, multi-center, pilot RCT using 2^3^ factorial design. The main objectives of the study are to assess the feasibility of targeting low- or high-normal PaCO_2_, PaO_2_, and MAP in comatose, mechanically ventilated patients after OHCA and to evaluate the effect of low- or high-normal PaCO_2_, PaO_2_, and MAP on brain injury markers at 48 h after cardiac arrest. Secondary objectives are to assess the effect of low- or high-normal PaCO_2_, PaO_2_, and MAP after OHCA on cerebral oxygenation, epileptic activity, and neurological outcome six months after cardiac arrest. COMACARE is a RCT comparing multiple treatment groups with each other. There is no additional control group not receiving any study interventions. The trial is unblinded; due to the nature of the interventions, the treating personnel cannot be blinded regarding study group allocations.

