#### Feasibility outcomes

Difference in PaCO2 between groups targeting low-normal (4.5-4.7 kPa) and high-normal (5.8–6.0) PaCO_2_
Difference in PaO2 between groups targeting low-normal (10–15 kPa) and high-normal (20–25 kPa) PaO_2_
Difference in MAP between groups targeting low-normal (65–75 mmHg) and high-normal (80–100 mmHg) MAPDistribution of values for primary and secondary outcomesRandomized/screened patient ratioConsent rateData completion rateRecruitment duration

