### Randomization and intervention

Schedule of enrolment, interventions, and assessments of the COMACARE trial are presented in Fig. 1. After ICU admission, participants are randomized into one of eight arms, with each arm having a different combination of PaCO_2_, PaO_2_, and MAP targets according to the 2^3^ factorial design:Low-normal PaCO_2_ (4.5–4.7 kPa), low-normal PaO_2_ (10–15 kPa), low-normal MAP (65–75 mmHg);High-normal PaCO_2_ (5.8–6.0 kPa), low-normal PaO_2_ (10–15 kPa), low-normal MAP (65–75 mmHg);Low-normal PaCO_2_ (4.5–4.7 kPa), high-normal PaO_2_ (20–25 kPa), low-normal MAP (65–75 mmHg);High-normal PaCO_2_ (5.8–6.0 kPa), high-normal PaO_2_ (20–25 kPa), low-normal MAP (65–75 mmHg);Low-normal PaCO_2_ (4.5–4.7 kPa), low-normal PaO_2_ (10–15 kPa), high-normal MAP (80–100 mmHg);High-normal PaCO_2_ (5.8–6.0 kPa), low-normal PaO_2_ (10–15 kPa), high-normal MAP (80–100 mmHg);Low-normal PaCO_2_ (4.5–4.7 kPa), high-normal PaO_2_ (20–25 kPa), high-normal MAP (80–100 mmHg);High-normal PaCO_2_ (5.8–6 kPa), high-normal PaO_2_ (20–25 kPa), high-normal MAP (80–100 mmHg).

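### Two of the three predefined serious adverse events count only if judged unexplained, an undefined causal call with no stated masked assessor in an unblinded trial

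*Protocol article*

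**What the plan says.** The section Data and safety monitoring opens its list with "The predefined serious adverse events (SAE) that could be related to the treatment interventions include" and then names three events:

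- A numeric one: "severe hypercapnia and respiratory acidosis (PaCO_2_ > 10 kPa and pH < 7.15".
- Two that carry a qualifier: "unexplained brain edema on CT scanning, and severe unexplained ARDS (PaO_2_/FiO_2_ ratio of < 100 mmHg".

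These events go into the study database and are reported to the principal investigators within 24 h. Where applicable, they also lead to interruption of the study intervention. A three-member data and safety monitoring board is named. Its access to the allocation and any role in adjudicating events are not described.

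Methods/Design states: "The trial is unblinded; due to the nature of the interventions, the treating personnel cannot be blinded regarding study group allocations". Randomization and intervention adds that target cards are placed at the bedside and on the ventilator. The oxygen comparison is set out under Feasibility outcomes: "Difference in PaO2 between groups targeting low-normal (10–15 kPa) and high-normal (20–25 kPa) PaO_2".

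**The concern.** A randomised safety comparison should count events first and discuss their cause afterwards. Here the cause is settled before the event qualifies.

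That matters more than usual in this population. Background begins with "Hypoxic ischemic encephalopathy is the leading cause of morbidity and mortality after out-of-hospital cardiac arrest", and later describes severe ischaemia-reperfusion injury with systemic inflammation. An explanation other than the allocated target will often be at hand for brain oedema or early respiratory failure, and the article gives no criterion for when such an explanation is enough. If the person judging knows the target, the threshold may also differ between levels.

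At stake is what the pilot can say about safety. The Discussion section says the results will inform whether a larger trial is justified, with separate papers on carbon dioxide, oxygen and MAP. Filtered counts could reassure falsely, or differ between levels for reasons unrelated to harm.

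**Working it through.** The plan gives no event-rate figure on this point, so there is nothing to reproduce. The check has three parts.

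**1. The definitions side by side**

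| Event | Numeric limit | Needs *unexplained* | Assessor stated |
|---|---|---|---|
| Hypercapnia with acidosis | PaCO2 > 10 kPa and pH < 7.15 | No | Not needed |
| Brain oedema on CT | None | Yes | No |
| Severe ARDS | PaO2/FiO2 < 100 mmHg | Yes | No |

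The qualifier is not needed to remove disease present at entry. Exclusion criteria already remove patients with a ratio below 100 mmHg, with intracranial pathology, or with suspected raised intracranial pressure. Masking is described elsewhere in Data collection: the near-infrared display is hidden from staff, and the six-month functional assessor is blinded. None is described for SAEs.

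Let *s* be the share of true events judged explained. The recorded fraction is 1 − *s*. With equal true rates at levels A and B, the ratio of recorded counts is (1 − *s*_A)/(1 − *s*_B), which equals 1 only if the judgement is applied equally at both levels. No value of *s* is in the article. It could lie anywhere from 0 (all recorded) to 1 (none recorded), so neither size nor direction can be given.

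**2. What the ARDS limit does and does not imply for the oxygen levels**

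Inputs: PaO2 targets of 10–15 and 20–25 kPa; FiO2 range of 21–100% (Randomization and intervention); 1 kPa = 7.50062 mmHg (unit constant). Ratio = PaO2 in mmHg / FiO2.

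- High-normal range: 20 × 7.50062 = 150.0 mmHg and 25 × 7.50062 = 187.5 mmHg. At FiO2 1.0 the ratio is 150–188, and it is higher at any lower FiO2. A ratio below 100 would need FiO2 above 150.0/100 = 1.50. It is therefore impossible *while PaO2 is in range*.
- Low-normal range: 10 × 7.50062 = 75.0 mmHg and 15 × 7.50062 = 112.5 mmHg. At 10 kPa the limit is met once FiO2 exceeds 75.0/100 = 0.75. At FiO2 1.0 it is met below 100/7.50062 = 13.3 kPa. It is therefore possible in part of the range.
- High-normal patient off target: the limit is met below 13.3 kPa at FiO2 1.0, below 0.9 × 13.33 = 12.0 kPa at FiO2 0.9, and below 0.8 × 13.33 = 10.7 kPa at FiO2 0.8.

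Now take the same lung at both levels. At the low-normal level, 10 kPa on FiO2 0.8 gives 75.0/0.8 = 94 mmHg, which meets the limit. At the high-normal level FiO2 goes to 1.0. If the ratio stays at 94 (a simplifying assumption), PaO2 is 94/7.50062 = 12.5 kPa, which is off target and also meets the limit.

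**3. What can be recovered without the label**

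Data collection stores blood gas results and ventilator settings for 48 h after ICU admission, 48 − 36 = 12 h beyond the longest intervention period. Gases are taken at least every 3 h, so a full 36 h intervention gives at least 36/3 = 12 samples. Both numeric limits can therefore be applied to all patients, including the 115 of 120 already enrolled. CT-reported oedema is not in that store.

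**The case against.** The strongest reply has four parts.

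- **The article is condensed.** The full protocol may define the term and name a masked assessor. The SAE list is introduced with a word that leaves it open, so it need not be exhaustive. This stands in part: a reader might infer that treating staff make the call and that explained events never reach the database, but the article says neither. It does state the definition itself, however, and the qualifier sits in that definition.
- **SAE counts are not a listed outcome.** They appear among neither the primary, secondary nor feasibility outcomes, and the section serves mainly as a rapid-reporting trigger. This stands, and it limits the weight of the point.
- **Low ratios are recoverable from stored data.** This also stands for the 48 h window. It is why the fix is cheap, but the article does not say such a derivation will be made.
- **Rewording the events could widen a trigger for interrupting treatment.** This stands, so the fix must be confined to recording and reporting.

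A stronger reading is tempting: that the ARDS limit cannot be met at the high-normal oxygen level, so that counts run against the low-normal level by arithmetic alone. The documents do not support it. Nothing requires PaO2 to be in range for an event to count, and a patient whose lungs are that poor leaves the range and meets the limit. The ratio may vary with the FiO2 in use, but nothing in the article sizes or signs a difference. The arithmetic also has no bearing on the carbon dioxide or MAP comparisons.

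Nor can it be asserted that CT is unscheduled, because the schedule is in a figure that is not shown.

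**Conclusion.** The point holds in a limited form. For two of three predefined SAEs, an undefined causal judgement is part of the event, no masked assessor is stated, and "the treating personnel cannot be blinded regarding study group allocations". Counts by randomised level are therefore open to under-counting and differential ascertainment. The hypercapnia event is numeric and is not affected.

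The conclusion rests on reading the definition as written and on no masked adjudication being arranged elsewhere. If the full protocol arranges it, the risk of differential ascertainment falls, but the under-counting of events judged explained remains. The size is unknown because the share judged explained is not given. Non-comparability of the oxygen levels is not shown. This is a worthwhile and inexpensive improvement to safety reporting; it does not undermine the trial's primary comparison.

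**What to change.** For recording and reporting only, leaving the interruption rule as it is:

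1. From the stored blood gases and ventilator settings, derive for every patient each PaO2/FiO2 below 100 mmHg and each PaCO2 above 10 kPa with pH below 7.15 in the 48 h window. Report both by randomised level for each of the three factors, and show FiO2 beside the ratio. Label the first as a ratio below the limit, since it is not by itself a diagnosis of ARDS.
2. Count every CT-reported brain oedema whatever its cause, and give the number of patients scanned at each level as denominator.
3. Put cause and relatedness in a separate field, completed by someone without knowledge of the allocation.

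With 115 of 120 patients enrolled, new prospective wording would reach only 120 − 115 = 5 patients, so the gain comes mainly from derivation and record review. The cost is a higher raw event count, one derived table, a search of CT reports and a short masked review.

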## Discussion

Trial recruitment began in Meilahti Hospital, Helsinki, in March 2016. Five additional Finnish centers joined the trial between May and December 2016 and Aarhus University Hospital joined the trial in March 2017. Participant recruitment is expected to be completed by December 2017 and the six-month neurological assessment is expected to be completed by June 2018. The study will be published as three separate papers comparing the effects of carbon dioxide, oxygen, and MAP on the primary and secondary outcomes. We aim to publish all the studies at the same time in the same journal. The results of the COMACARE trial will provide preliminary clinical evidence regarding the feasibility of targeting low- or high-normal values of PaCO_2_, PaO_2_, and MAP in comatose patients after cardiac arrest and resuscitation. It will also provide preliminary information on the effect of low- or high-normal levels of PaCO_2_, PaO_2_, and MAP on neurological injury biomarker concentrations, brain oxygenation, and epileptic activity. The results of this trial will be used to evaluate whether a larger RCT on this subject that is sufficiently powerful to determine the effects of low- or high-normal levels of PaCO_2_, PaO_2_, and MAP on survival and neurological recovery at six months is justified (Additional file 1).

## Trial status

Recruitment is active in all six study sites in Finland and in one study site in Denmark. Currently, 115 patients have been included.

## Abbreviations

CBF: Cerebral blood flow
EEG: Electroencephalogram
GCS: Glasgow coma scale
GPD: Generalized periodic discharging
ICU: Intensive care unit
MAP: Mean arterial pressure
NIRS: Near-infrared spectroscopy
NSE: Neuron-specific enolase
OHCA: Out-of-hospital cardiac arrest
PaCO_2_: Arterial carbon dioxide tension
PaO_2_: Arterial oxygen tension
PEEP: Positive end-expiratory pressure
ROSC: Return of spontaneous circulation
VF: Ventricular fibrillation
VT: Ventricular tachycardia
